### Interim Analysis

A single interim efficacy analysis is planned when 50% of the study endpoints have occurred; or at 3.5 years of follow-up, whichever occurs first. The DSMC will be asked to advise on early discontinuation of the trial at this point if there is clear evidence of benefit or harm in the treatment arm as defined below, using a two-sided statistical significance threshold of 0.0054 and power of 80%[70]. This analysis will have sufficient power to determine whether the intervention arm can expect a prolongation of the primary outcome from 2 years to 3.42 years. Based on the modest impact of HSV-2 and valacyclovir on HIV viral load, it is unlikely that such clear evidence of benefit will be seen at this interim analysis.

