### Sample Size Calculation

It is hypothesized that suppression of HSV-2 using valacyclovir will increase the time until participants' CD4 counts reach ≤ 350 cells/mm^3 ^or initiate HAART from the expected value of 2 years to 2.75 years (see justification below). Participants will be recruited over 2 years and followed over 3 years. Using a conservative estimate that 25% of the sample will be lost to follow-up on average half way through the 3-year follow-up period, the expected years of follow-up is 0.75 × 3 years + 0.25 × 1.5 years = 2.625 years overall. In order to detect a difference of 0.75 years with a two-sided α = 0.0492 (adjusted for multiple analyses by the method of O'Brien and Fleming)[70] and 80% power in a survival analysis, 240 individuals will be required in each study arm, or 480 participants overall[71].

The expected rate at which HIV disease would progress in HAART-untreated individuals was based on both a retrospective review of patient charts and the published literature. Among 142 patients with at least 3 CD4 counts before starting HAART, with baseline CD4 count > 400 cells/mm^3 ^at the Toronto General Hospital Immunodeficiency Clinic, the median time from first presentation to reaching CD4 ≤ 350 cells/mm^3 ^was 2.0 years ([name], [name]: personal communication). In the subset with higher baseline CD4 counts (> 500 cells/mm^3^), the median time was 2.5 years. Consistent with these findings, a published retrospective observational cohort study of 4268 HIV-infected individuals in the United Kingdom with baseline CD4 counts > 500 cells/mm^3 ^also found the median time to until reaching CD4 counts ≤ 350 cells/mm^3 ^or initiation of antiretroviral therapy was 2.5 years[72]. Both are consistent with the generally accepted rate of CD4 count decline of 50-60 cells/mm^3 ^per year[2,3].

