### Primary Analysis

The primary outcome of the trial is the time from baseline until reaching the primary endpoint, a composite of either a CD4 cell count ≤ 350 cells/mm^3 ^measured on two consecutive occasions at least 1 month apart, or initiation of HAART for any reason, whichever occurs first. The primary analysis will be a proportional hazards model, stratified by site, which will estimate the relative risk of progression to this endpoint associated with valacyclovir. Participants who do not reach either endpoint will be censored at the date of last CD4 count. The primary analysis will be conducted at the conclusion of the trial using the α = 0.0492 level of significance. This significance level adjusts for one interim analysis of the data according to the method of O'Brien and Fleming[70].

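### The O'Brien-Fleming thresholds 0.0054 and 0.0492 rest on a slightly small constant: with one look at 50% of endpoints they spend 0.0513, against an implied 0.05

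*Protocol article*

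**What the plan says.** The Interim Analysis section fixes the number and timing of looks: "A single interim efficacy analysis is planned when 50% of the study endpoints have occurred; or at 3.5 years of follow-up, whichever occurs first". Benefit or harm is then to be judged by the DSMC "using a two-sided statistical significance threshold of 0.0054 and power of 80" percent.

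The Primary Analysis section fixes the final test: "The primary analysis will be conducted at the conclusion of the trial using the α = 0.0492 level of significance". It then explains the figure: "This significance level adjusts for one interim analysis of the data according to the method of O'Brien and Fleming". The Sample Size Calculation section uses the same level, "two-sided α = 0.0492 (adjusted for multiple analyses by the method of O'Brien and Fleming").

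None of these sections states the overall type I error. A final level just under 0.05, described as adjusted for one interim look, implies 0.05 two-sided. None of them says what happens to 0.0054 or 0.0492 if the look falls at a share of endpoints other than 50%.

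**The concern.** A two-look design has to be checked as a pair. A final level of 0.0492 gives up only 0.0008 of an overall 0.05, although the interim look uses 0.0054. The two tests are correlated, so the interim cost is partly shared, but the saving has to be large enough to cover the gap. If it is not, the trial tests its primary endpoint at an error rate above the one that the O'Brien-Fleming attribution leads a reader to expect, and a borderline final result could be called significant without full support.

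**Working it through.** **Inputs.** Interim level 0.0054 two-sided (Interim Analysis); final level 0.0492 two-sided (Primary Analysis, Sample Size Calculation); one look at 50% of endpoints (Interim Analysis). Assumed: overall two-sided alpha 0.05.

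**Step 1: z-values and shape.** 0.0054 gives z1 = 2.7822; 0.0492 gives z2 = 1.9669. For one look at information fraction t, an O'Brien-Fleming boundary has z1 = c/√t and z2 = c. At t = 0.5 the ratio should be √2 = 1.4142. The plan's ratio is 2.7822/1.9669 = 1.4145. The shape is therefore right, with c = 1.967.

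**Step 2: error spent by the stated pair.** Under the null hypothesis Z1 and Z2 are bivariate normal with correlation √t = √0.5 = 0.7071. Then

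1 − P(|Z1| < 2.7822 and |Z2| < 1.9669) = 0.0513.

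Of this, 0.0054 is spent at the interim, and 0.0513 − 0.0054 = 0.0459 is added at the end. The excess over 0.05 is 0.0013.

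**Step 3: the constant that gives 0.05.** Solving 1 − P(|Z1| < c√2 and |Z2| < c) = 0.05 at t = 0.5 gives c = 1.9774. The boundaries are z = 2.7965 and 1.9774, that is p = 0.0052 and 0.0480.

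- If 0.0054 is kept at the interim, the final level that holds 0.05 is 0.0479.
- If 0.0492 is kept at the end, the interim level has to be 0.0026.
- Lan-DeMets O'Brien-Fleming-type spending at 50% gives 0.0031 and 0.0490, so it does not reproduce the stated pair either.

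**Step 4: other information fractions.** With 0.0054 and 0.0492 held fixed:

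| Share of final endpoints at the interim | Overall two-sided error |
|---|---|
| 50% | 0.0513 |
| 60% | 0.0506 |
| 70% | 0.0500 |
| 80% | 0.0495 |

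The stated pair holds 0.05 only from about 70% upwards.

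**Step 5: cost of correcting the final level.** The planned effect is a change "from the expected value of 2 years to 2.75 years", a hazard ratio of 2/2.75 = 0.727 if times are exponential. Schoenfeld's formula is D = 4(z for alpha + z for power)² / (ln HR)², with (ln 0.727)² = 0.1014 and z for 80% power = 0.8416.

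- At 0.0492: 4 × (1.9669 + 0.8416)² / 0.1014 = 311 events.
- At 0.0480: 4 × (1.9774 + 0.8416)² / 0.1014 = 313 events.

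At a fixed 312 events, power falls from 80.1% to 79.8%.

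**The case against.** The strongest reply is that the plan names a recognised method and uses its shape correctly, that the source of the constants is a cited reference we cannot see, and that an excess of 0.0013 has no practical effect on sample size or conduct. Most of this stands. It would be wrong to say that the pair is not O'Brien-Fleming: only the constant is slightly small. It is also true that 0.05 is inferred. What does not stand is that the final level adjusts for the interim look as stated, because no variant tried brings the pair to 0.05 at a 50% look.

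A reader might infer something stronger from the 3.5-year trigger: that an early calendar look would inflate the error well beyond 0.0513. The documents do not support this. With uniform accrual over the planned 2 years, exponential times and the plan's 2 and 2.75 years, half of the 5-year endpoints arrive at about 2.2 to 2.5 years, so the endpoint trigger comes first. Even with much slower progression, a constant hazard puts at least 63% of the 5-year endpoints before 3.5 years (77% at a median of 2 years). The overall error at those fractions is about 0.0505 or less. A look well below 50% of the final endpoints would need a strongly rising hazard together with much slower progression than planned.

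A reader might also object that 50% of the endpoints has no stated target count behind it. A journal article may leave that figure to the full protocol or SAP, so it is not a defect here.

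**Conclusion.** The point holds as a small numerical error in the confirmatory threshold. At a look at exactly 50% of endpoints, 0.0054 and 0.0492 spend 0.0513 instead of 0.05, because the boundary constant is 1.967 where 1.977 is needed. This rests on an overall two-sided alpha of 0.05, which the article implies but does not state, and on the usual bivariate normal approximation. Under the corrected pair, a final p-value between about 0.0480 and 0.0492 is the only final result that would be read differently. The sample size ("240 individuals will be required in each study arm, or 480 participants overall") is not called into question by this point. The figures are worth correcting because they decide the primary result and are easy to change before the data are seen.

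**What to change.** 1. In the Sample Size Calculation, Interim Analysis and Primary Analysis sections, state the overall two-sided alpha. If it is 0.05 and the look is at 50% of endpoints, replace 0.0054 and 0.0492 with 0.0052 and 0.0480, or keep 0.0054 and replace 0.0492 with 0.0479.
2. In the same sections, state that if the share of endpoints at the interim differs from 50%, the final level will be recomputed from the share actually observed (interim endpoints divided by final endpoints), so that the overall error stays at its stated value. This share is known once the trial ends at its fixed date, so the rule needs no event-driven stopping.

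The cost is two figures and one sentence, and about 2 more events (311 to 313 by Schoenfeld), or about 0.3 points of power if the number of events is left as it is.

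### At half of the endpoints implied by the 480-participant design, the interim look has about 72% power for a prolongation from 2 to 3.42 years, not the stated 80%

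*Protocol article*

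**What the plan says.** The Interim Analysis section fixes the timing of the look: "A single interim efficacy analysis is planned when 50% of the study endpoints have occurred; or at 3.5 years of follow-up, whichever occurs first". The test at that look is described as "using a two-sided statistical significance threshold of 0.0054 and power of 80" per cent, and the section says that power suffices for a "prolongation of the primary outcome from 2 years to 3.42 years". It adds that so large a benefit is unlikely to be seen then.

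The final design is in the Sample Size Calculation section. The target is an increase in time to endpoint "from the expected value of 2 years to 2.75 years". The test and size are given as "In order to detect a difference of 0.75 years with a two-sided α = 0.0492" and "80% power in a survival analysis, 240 individuals will be required in each study arm, or 480 participants overall". Follow-up is reduced for loss, on the assumption that "25% of the sample will be lost to follow-up on average half way through the 3-year follow-up period", which the article turns into 2.625 expected years. The 2-year control value is supported by a median time of 2.0 years in a chart review.

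Neither section gives a number of endpoints for the final or the interim analysis.

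**The concern.** The interim section ties three things together: an information fraction (half of the endpoints), a significance level with a power, and a detectable effect. In a time-to-event comparison, the number of events, the significance level and the effect determine the power. So once the design fixes the total number of endpoints, the interim statement can be checked.

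The statement matters because it is the only operating characteristic given for the single efficacy look that the monitoring committee will have. If it is too favourable, the committee would believe that a non-significant interim result argues against an effect of that size more strongly than it does. At 72% power the look misses the named effect about 28% of the time, not 20%.

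**Working it through.** **Inputs from the article.** Interim: two-sided 0.0054, 80% power, 2 vs 3.42 years, half of the endpoints. Final: two-sided 0.0492, 80% power, 2 vs 2.75 years, 240 per arm, 2 years of accrual, 2.625 years of loss-adjusted follow-up. **Assumptions added here:** exponential times, the stated years read as medians, uniform accrual, and 2.625 years taken as follow-up after accrual closes. The endpoint total is derived, not quoted.

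**Step 1. Reproduce the plan's sample size.** For 1:1 allocation the Schoenfeld formula is

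events = 4 × [(z for alpha + z for power) / ln(ratio of medians)]².

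Final analysis: z = 1.967 and 0.842, and ln(2.75/2) = 0.3185. Events = 4 × (2.808/0.3185)² = 311.1, so 312.

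With accrual A = 2, further follow-up F = 2.625 and hazard λ = ln 2/median, the probability of an endpoint is

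1 − [exp(−λF) − exp(−λ(A+F))]/(λA).

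- Median 2 years: 0.710.
- Median 2.75 years: 0.595.
- Average median of 2.375 years: 0.648.

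Using the average median, N = 311.1/0.648 = 480, or 240.1 per arm, which is the plan's figure. Arm-specific probabilities average 0.652 and give N = 311.1/0.652 = 477. At N = 480 they give about 240 × (0.7096 + 0.5947) = 313 endpoints. The design thus implies about 312 endpoints, and half is about 156.

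**Step 2. Events that the interim statement needs.** z = 2.782 and 0.842, and ln(3.42/2) = ln 1.71 = 0.5365. Events = 4 × (3.624/0.5365)² = 182.5, so 183. The Freedman formula gives 192.

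**Step 3. Power at the interim.** With d events, power = Φ(0.5365 × √d/2 − 2.782). The effect detectable with 80% power is 2 × exp(2 × 3.624/√d) years.

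| Interim events | Basis | Power for 3.42 years | Detectable at 80% power |
|---|---|---|---|
| 156 | Half of 312 | 0.715 | 3.57 years |
| 157 | Half of 313 | 0.72 | 3.57 years |
| 165 | Half of 330: 2 + 3 years, no loss | 0.75 | 3.52 years |
| 183 | Needed for the statement | 0.80 | 3.42 years |

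At 156 events: 0.5365 × 12.49/2 = 3.350, and Φ(3.350 − 2.782) = 0.715. The hazard ratio detectable at 80% power is 2/3.57 = 0.56, against 2/3.42 = 0.585 in the plan.

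**Step 4. Check by simulation.** Log-rank tests on 4,000 simulated trials (2 vs 3.42 years, uniform accrual, 25% exponential loss by 3 years) gave power 0.71 at 157 events and 0.80 at 183.

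**Step 5. The 3.5-year limb.** The earlier of the two triggers applies, so this limb can never add events beyond the 50% point. In simulation under the planned effect, the 157th event falls at about 2.5 calendar years, so the 50% trigger comes first.

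**The case against.** **The total is derived.** The article never states an endpoint total, so any interim count is an inference. That is true, and it is why the figure rests on the one set of assumptions that returns 480 participants.

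**Some readings bring power close to 80% or above.**
- Treating 2 and 2.75 years as means, with 2 + 3 years and no loss, gives 194 interim events and 83% power. That design would need only about 385 participants, it ignores the stated 25% loss, and the 2-year value rests on a median.
- Half of the endpoints expected with no loss and no treatment effect is 179 events, with 79% power. This sets aside both the planned effect and the planned loss.
- Reading the trigger as half of the participants gives 240 events and more than 80% power, but the trigger is worded in endpoints.

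None of these fits the text.

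**The consequence is small.** This objection stands. The detectable value moves from 3.42 to about 3.57 years, roughly two months. The sentence describes the look and does not govern it: the committee acts on the 0.0054 threshold. Both effects lie well beyond the planned hazard ratio of 2/2.75 = 0.727, and the article itself does not expect clear benefit at this look.

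**Stronger inferences that the article does not support.** A reader might put the power as low as 61%. That comes from 130 events, which assumes that everyone is followed for exactly 2.625 years; such a design would need about 577 participants, not 480. A reader might also conclude that 0.0054 was used one-sided, because 3.42 years then needs only 160 events, close to half of the implied total. The coincidence justifies asking for confirmation, but the article says two-sided and does not show how 3.42 was obtained, so no cause can be asserted.

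**Conclusion.** The concern holds, as a minor point. At about 156 events, the look has about 72% power for 2 vs 3.42 years at two-sided 0.0054, not 80%. It falls about 27 events short of the 183 needed (183 − 156). With 3 years of further follow-up and no loss, power is still only about 75%. If the true medians were 2 and 3.42 years and the trigger were half of the endpoints then expected, the count would be about 147 and power about 68%, so 72% is not a pessimistic figure.

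The result rests on exponential times, medians of 2 and 2.75 years, uniform 2-year accrual and 2.625 years of further follow-up, which together reproduce the stated sample size.

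It would be wrong to infer that the stopping boundary, the type I error control or the final sample size is at fault. The sample size reproduces, and the boundary and final alpha do not depend on the sentence in question.

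**What to change.** In the Interim Analysis section, state the planned number of endpoints (about 312) and the count that triggers the look (about 156). Then do one of two things: restate the effect detectable with 80% power as about 2 to 3.6 years (hazard ratio about 0.56), or keep 3.42 years and give the power as about 72%. Confirm that 0.0054 is two-sided. If the sponsor's own calculation used other assumptions, give them with the resulting event total so that both sections can be reproduced.

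The cost is one or two sentences and a slightly less favourable interim figure. No participants are added, and the 0.0054 threshold, the 50% or 3.5-year trigger, the final 0.0492 and the 480 participants all stay as they are.

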### Primary Analysis

The primary outcome of the trial is the time from baseline until reaching the primary endpoint, a composite of either a CD4 cell count ≤ 350 cells/mm^3 ^measured on two consecutive occasions at least 1 month apart, or initiation of HAART for any reason, whichever occurs first. The primary analysis will be a proportional hazards model, stratified by site, which will estimate the relative risk of progression to this endpoint associated with valacyclovir. Participants who do not reach either endpoint will be censored at the date of last CD4 count. The primary analysis will be conducted at the conclusion of the trial using the α = 0.0492 level of significance. This significance level adjusts for one interim analysis of the data according to the method of O'Brien and Fleming[70].

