HSV-2 is among the most common co-infections in HIV, with a prevalence of 52-95%,[11-16] and several important interactions have been observed between these two viruses. First, HSV-2 is associated with increased HIV acquisition and transmission, even in asymptomatic individuals[17-27]. Recent trials of daily acyclovir for HSV-2 suppression, however, did not show a benefit on decreasing HIV acquisition or transmission[28-30]. Persistence of HIV target cells in the genital tract, suboptimal dosing and inadequate adherence may have contributed to the negative results[31]. Second, both symptomatic, clinical recurrences of HSV-2, and asymptomatic shedding of HSV-2 have been clearly associated with increased HIV levels in both genital secretions and plasma[32-35]. Upregulation of HIV replication by HSV gene products such as infected cell protein (ICP)-0, ICP-4, ICP-27 and Us11, and stimulation of the NF-Kappa B pathway may contribute to these increases in HIV viral load[36-40]. Further, clinical trials using both acyclovir and valacyclovir suppressive therapy in co-infected individuals, including 20 men who have sex with men (MSM) in Peru, 140 women in Burkina Faso, and 67 women in Thailand have demonstrated clinically significant, reciprocal decreases in HIV RNA viral load of 0.33-0.53 log_10_[41-43].

The plasma HIV viral load, in turn, is the major predictor of CD4 cell decline and HIV disease progression, and viral load strata that increase by about 0.5 log copies/mL correlate with increased rates of CD4 decline of roughly 10 cells/mm^3^/year[2-5]. It follows, then, that HSV-2 suppressive therapy might delay HIV disease progression in HAART-untreated individuals through its effects on the HIV viral load. Indeed, a meta-analysis from the pre-HAART era suggested that > 3200 mg per day of acyclovir offered a significant survival benefit (incidence rate ratio for mortality, 0.81, 95%CI 0.68-0.96), although this effect was largely related to treatment of active herpesvirus disease in individuals with late-stage HIV/AIDS[44]. More recently, the multicentre Partners in Prevention trial from Sub-Saharan Africa has shown that acyclovir 400 mg twice daily was associated with moderately decreased progression to the composite endpoint of CD4 < 200 cells/mm3, HAART initiation, or non-trauma related death (hazard ratio = 0.84, 95%CI 0.71-0.98)[45].

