### Randomization and blinding methods

Randomization is stratified by site in permuted blocks of variable size (4 and 6) using a computer-generated list of random numbers. The CTN created and coordinated the allocation sequence, and randomization is performed through a secure website which ensures allocation concealment. All participants and study personnel (including investigators, research coordinators, data analysts) will be blinded to treatment allocation throughout the trial. Access to the allocation code will be restricted to one study statistician who will not perform the final study analyses.

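### The stated primary Cox model is valid but names no baseline covariate, although the protocol itself treats baseline CD4 count and viral load as prognostic; some power is given up

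*Protocol article*

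**What the plan says.** The Primary Analysis section of the protocol article states: "The primary analysis will be a proportional hazards model, stratified by site". It adds the censoring rule and the final significance level, and names no covariate. Under Randomization and blinding methods, site is the only stratification factor. The Secondary Analyses section names no adjusted analysis of the primary outcome. The Subgroup Analyses section looks at HSV-1 serostatus, adherence and country, not at baseline CD4 or viral load.

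Elsewhere the article treats both variables as prognostic:

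- **Viral load.** Background: "The plasma HIV viral load, in turn, is the major predictor of CD4 cell decline and HIV disease progression". The same paragraph ties a step of about 0.5 log to roughly 10 cells/mm³ per year of extra decline.
- **Baseline CD4.** Eligibility allows 400 to 900, and the endpoint threshold is 350. Under Sample Size Calculation, the clinic chart review gives a median of 2.0 years to 350 for patients starting above 400. It then continues "In the subset with higher baseline CD4 counts" (above 500) with a median of 2.5 years.

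**The concern.** A Cox hazard ratio is not collapsible. If a strong predictor of the event time is left out, the treatment hazard ratio moves toward 1 even under perfect randomisation, and the test loses power. Here one candidate predictor is the starting value of the variable whose threshold defines much of the endpoint, and eligibility already requires that it be measured.

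Two things are at stake. The first is power for a modest expected effect. The second is avoidable noise: if baseline CD4 has a standard deviation of 100 to 144 (an assumption; 144 is 500/√12, for a uniform spread over 400 to 900), the standard error of the between-arm difference in mean CD4 is SD × √(2/240), or 9 to 13 cells. The drug is assumed to save 10 cells per year, so a one-standard-error imbalance is about the size of one year's assumed benefit.

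**Working it through.** **Inputs from the article.** "In order to detect a difference of 0.75 years with a two-sided α = 0.0492"; "80% power in a survival analysis, 240 individuals will be required in each study arm, or 480 participants overall"; effect "or initiate HAART from the expected value of 2 years to 2.75 years"; expected follow-up 2.625 years; 1:1 allocation. On exponential times the hazard ratio is 2/2.75 = 0.727.

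**1. The plan's own figure.** Events needed are 317 (Freedman) or 312 (Schoenfeld).

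- *2 and 2.75 years read as means:* event probability over 2.625 years = [(1 − e^(−2.625/2)) + (1 − e^(−2.625/2.75))]/2 = 0.673. Then 317/0.673 = 471, or 236 per arm, within 3% of 480. The figure reproduces.
- *Read as medians with 2.625 years:* event probability 0.541, total 577 (Schoenfeld) or 586 (Freedman), and power at 480 is 72.5%.
- *Read as medians with 3.5 years* (0.75 × 4 + 0.25 × 2, using a mean of 4 years under 2-year accrual): event probability 0.644, and 312/0.644 = 484.

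None of these calculations uses a covariate.

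**2. Effect of omitting a covariate, by its strength.** The strength is the standard deviation (SD) of the prognostic part of the log hazard, which the documents do not give. Simulation: 480 participants, exponential times, 3.5 years of follow-up, α = 0.0492, 1,500 trials per row, no site strata, hazard ratio 0.727 conditional on the covariate.

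| SD of log hazard | Power unadjusted | Power adjusted | Gain (points) | Mean HR unadjusted |
|---|---|---|---|---|
| 0.2 | 78.7% | 80.1% | +1 | 0.728 |
| 0.3 | 75.7% | 79.3% | +4 | 0.735 |
| 0.4 | 72.5% | 78.0% | +5.5 | 0.746 |
| 0.5 | 69.8% | 77.9% | +8 | 0.749 |
| 0.6 | 64.7% | 76.1% | +11.5 | 0.760 |

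With 1,500 trials the Monte Carlo standard error of a power near 70% is √(0.7 × 0.3/1500) = 1.2 points.

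**3. Calibrating CD4 to the protocol's medians.** The log-linear CD4 effect was chosen so that the whole group has a median of 2.0 years and those above 500 a median of 2.5 years. The CD4 distribution is not given, so three were assumed on 400 to 900.

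| Assumed CD4 distribution | Share above 500 | SD of log hazard | 2.625 years: unadjusted → adjusted | 3.5 years: unadjusted → adjusted |
|---|---|---|---|---|
| Right-skewed (400 + exponential, mean 150) | 50% | 0.28 | 69.6 → 72.5% (+3) | 77.7 → 81.7% (+4) |
| Truncated normal (550, SD 130) | 74% | 0.51 | 66.9 → 74.1% (+7) | 69.8 → 77.7% (+8) |
| Uniform | 80% | 0.60 | 63.4 → 73.9% (+10.5) | 64.8 → 78.9% (+14) |

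The gain from CD4 alone is therefore about 3 to 14 points.

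**4. If 0.727 is taken as the unadjusted (marginal) ratio instead.** At 3.5 years, adjustment raises power from 80.0 to 82.9% at SD 0.3 and from 78.7 to 86.1% at SD 0.5. The gain is of similar size, but it then comes on top of the planned power.

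**5. Limit of the calibration.** The chart medians concern CD4 ≤ 350 alone. The trial endpoint also counts HAART begun for pregnancy, hepatitis B or preference, which depends less on CD4. This favours the lower part of the range.

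**The case against.** The strongest reply is that this is a preference about efficiency, not an error. A site-stratified model matches site-stratified randomisation, holds its type I error and contradicts nothing in the article. The sample size was set without covariates for a population-level contrast of 2 against 2.75 years. On that reading, omitting covariates takes nothing from the planned 80%; adjusting would only add to it. Chance imbalance in CD4 is sampling variation that the standard error already covers, not bias. An analysis plan that is not shown may list covariates. All of this stands, and it sets the level of the point. It does not remove the gain that adjustment offers over the model as stated.

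Three stronger readings are tempting and are not supported:

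- *That dividing the distance to 350 by 50 to 60 cells per year shows a spread from about 1 year (start at 400) to about 10 years (start at 900).* By that arithmetic nobody starting above 500 would reach 350 before (500 − 350)/60 = 2.5 years. Yet 2.5 years is the reported median in that group, so the straight line overstates the dependence.
- *That these are the dominant predictors.* The article says major, and only of viral load. The role of baseline CD4 is inferred from the two medians.
- *That adjustment is free.* It changes the hazard ratio to a conditional one. A baseline viral load is only implied, through the elite-controller exclusion; the listed viral load outcomes are at 12, 24 and 36 months.

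**Conclusion.** The point holds as a weakness of efficiency in the stated primary model. The analysis is valid, but it leaves unused at least one baseline measurement that every participant must have and that the protocol's own figures show to be prognostic.

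The size cannot be derived from the documents. A reader might want a single narrow figure for the lost power, but that would rest on slope variation, assay noise and rates of elective HAART that appear nowhere in the article. What can be said is conditional: about 3 to 14 points for CD4 alone if the chart medians carry over to this population, and as little as 1 point if the covariates are weak. The endpoint's HAART component pulls the gain down. A reader might also infer that the unadjusted result would be biased or invalid; it would not be.

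**What to change.** Before unblinding, and preferably before the interim look so that both looks use the same model, specify the primary analysis as a Cox model stratified by site and adjusted for:

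- continuous baseline CD4, taken as the qualifying count within 4 weeks of starting the trial (the other qualifying count has no stated age limit, so an average of the two could include an old value);
- baseline log10 HIV viral load, where a pre-treatment value is collected.

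State the functional form of each term in advance. Keep the unadjusted site-stratified model as a sensitivity analysis. If an existing analysis plan already lists covariates, bring the protocol statement into line with it.

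The cost is a sentence or two of text and no extra participants. The reported hazard ratio becomes conditional on the covariates, and the report should say so.
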